## Abstract

**Background:**

Current international consensus is that ‘early’ referral to palliative care services improves cancer patient and family carer outcomes. In practice, however, these referrals are not routine. An approach which directly addresses identified barriers to early integration of palliative care is required. This protocol details a trial of a standardized model of early palliative care (Care Plus) introduced at key defined, disease-specific times or transition points in the illness for people with cancer. Introduced as a ‘whole of system’ practice change for identified advanced cancers, the key outcomes of interest are population health service use change.

The aims of the study are to examine the effect of Care Plus implementation on (1) acute hospitalisation days in the last 3 months of life; (2) timeliness of access to palliative care; (3) quality and (4) costs of end of life care; and (5) the acceptability of services for people with advanced cancer.

**Methods:**

Multi-site stepped wedge implementation trial testing usual care (control) versus Care Plus (practice change). The design stipulates ‘control’ periods when usual care is observed, and the process of implementing Care Plus which includes phases of *planning, engagement, practice change and evaluation*. During the practice change phase, *all* patients with targeted advanced cancers reaching the transition point will, by default, receive Care Plus.

Health service utilization and unit costs before and after implementation will be collated from hospital records, and state and national health service administrative datasets. Qualitative data from patients, consumers and clinicians before and after practice change will be gathered through interviews and focus groups.

**Discussion:**

The study outcomes will detail the impact and acceptability of the standardized integration of palliative care as a practice change, including recommendations for ongoing sustainability and broader implementation.

**Trial registration:**

Australian New Zealand Clinical Trials Registry ACTRN 12619001703190. Registered 04 December 2019.

## Background

People living with cancer suffer a significant personal burden of symptoms, and have needs for psychological support, as well as better care and information for their families as they navigate their illness [1, 2]. For example, over 50% of patients with advanced cancer report pain, fatigue and shortness of breath, and their families commonly report anxiety and inadequate assistance as they seek to provide support [3]. Both patients and their families report a preference for more information about the illness, its course and the future more broadly in order to plan and make decisions accordingly [1, 3]. However, specific attention to these needs is variable, with oncologists reporting inadequate time, expertise and clinic space to adequately identify and respond to such needs [4, 5].

People with advanced cancer are high users of health care services. Studies of patients in Victoria, Australia who died with cancer reveal that following a diagnosis of incurable disease, people can expect to have a median of three multiday hospital admissions, and spend a total of 29 days in hospital in their final months of life [6–8]. Most (80%) will die in hospital, including 57% in an acute setting. The high levels of healthcare utilization, including at the end of life, have significant cost implications. A study of costs incurred between the period 2009–2013 determined that the average cost of care per cancer case was $49,733 in the last year of life [9], with 80% of these costs due to hospitalisations [10].

Early palliative care is a high value proposition – where value is defined as outcomes that matter to patients and the cost needed to achieve these outcomes [11]. The goals of palliative care are to improve health outcomes for patients with advanced cancer AND to deliver high quality care at lower cost. A significant evidence-base exists (Table 1) to support the systematic implementation of timely palliative care in routine cancer care to reduce variation in care, improve patient outcomes, and reduce health system burden and cost. These benefits have led a number of professional organisations including the American Society of Clinical Oncologists and European Society of Medical Oncologist to recommend that *inpatients and outpatients with advanced cancer should receive dedicated palliative care services, early in the disease course, concurrent with active treatment.”* [28, 29].

**Table 1 Tab1:** *Palliative care: A high value proposition where value = patient outcomes achieved relative to cost* [11]

***Patient benefits:*** Randomized control trials involving more than 2500 patients with advanced cancer demonstrate improved QOL, symptoms, mood, communication, satisfaction with care & survival [12–21].	
***Family carer benefits:*** Evidence demonstrates improved health outcomes, mood, and satisfaction and survival [17, 22]	
***Health Service Benefits:*** Earlier palliative care referrals are associated with 70% greater likelihood of death outside hospital - the preferred option of most patients [23], fewer emergency presentations (48% vs 68%; *P* < .001), & hospital admissions (52% vs 86%; P < .001) [24, 25].	
***Reduced cost*****:** Evidence from systematic reviews report costs savings of $4251 per patient and simultaneous improvement of quality of care [26]	
***Timing of palliative care is important to realise benefits:*** incremental advantages according to length of engagement with palliative care; > 2 weeks before death associated with reduced hospital death (*P* < 0.001), more than 4 weeks with fewer emergency presentations (≥4 weeks, P < 0.001) [24]. Expert consensus suggests referral should occur ≥3 months before death [27].	

Despite evidence of benefit and recommendations for best practice, only 59% per cent of 29,680 cancer inpatients in Victoria, Australia accessed any palliative care in their last year of life [7]. Of those who did access palliative care, this occurred very late – a median of 27 days before death [7]. For 61%, the first palliative care consultation occurred in the final hospital admission which concluded with death. Patients in this cohort had at least one (83%) or two or more (38%) indicators of poorer quality of end of life care [7], defined as more than 14 days in hospital, more than one acute admission or Emergency Department presentation in the last 30 days of life [30]. Further, while people consistently express a preference to die at home [31], only 20% of Victorian cancer patients in this study died at home. Conversely, in a cohort of people with high grade glioma, those who accessed timely palliative care had a 70% greater chance of death at home [23].

Several barriers to early palliative care integration have been identified and include: (1) patients and clinicians viewing palliative care as care of the imminently dying [32, 33]; (2) uncertainty about when to refer; (3) lack of relationships and confidence in the quality of palliative care service; and (4) capacity of community-based palliative care services to respond to demand [34]. There is growing evidence for the efficacy of outpatient palliative care services in addressing many of these barriers, particularly services that are integrated with oncology outpatient clinics. Notably, outpatient clinics facilitate early engagement with palliative care as they provide access to patients in usual care settings and are ‘culturally’ consistent with ongoing cancer therapy [34]. Outpatient palliative care is also associated with improved satisfaction among clinicians including referring oncologists as they facilitate clinician relationships of trust, expedite engagement with community care, and are proven to be effective with improved patient and health service outcomes [35, 36].

Fundamental to the routine integration of palliative care for patients with advanced cancer is to address clinician uncertainty around timing of palliative care referrals. Transition points – which are readily recognizable, objective points within a cancer illness course, have been endorsed by an international expert Delphi consensus as a key element of standardizing palliative care referrals and thus, reducing variation in care [37]. Previous research on the health care use of Victorian patients with high grade glioma (HGG) and metastatic breast, prostate as well as lung cancers demonstrated clear disease-specific transition points (e.g. multiday admission with metastatic disease) in the illness trajectories, which heralded subsequent increased health service utilisation and poor prognosis [7]. Preliminary data from a current phase 2 randomised control trial (RCT) of early palliative care introduction reveals that definitions of transition points vary across cancer types [38], and therefore a ‘one-size-fits all’ approach to early palliative care in cancer illness cannot be applied. Preliminary data from this study [38] also reveals feasibility and acceptability of early palliative care to both patients and health professionals.

Drawing on the evidence presented thus far, combined with the body of evidence accrued by the research team on the nature of current practice and needs – including evaluations of feasibility and effectiveness of responses [6–8, 32, 33, 38, 39], this study aims to develop and implement a population-based intervention called *Care Plus* to reduce hospital admissions at the end of life – consistent with the preferences of most patients.

The development of this study was guided by the UK Medical Research Council methodological framework for developing complex interventions, and the study objectives will be evaluated in accordance to the core domains of the RE-AIM evaluation framework – Reach, Effectiveness, Adoption, Implementation and Maintenance [40].

### Objectives

Primary Objective: To reduce acute hospitalisation days in the last 3 months of life for people with advanced cancer (Effectiveness).

#### Secondary objectives

To improve timely access to early palliative care, defined as first contact at least 90 days before death, for people with advanced cancer (Reach)To improve quality of end of life care for patients with cancer, with reduced acute health system use (Effectiveness)To assess the acceptability of *Care Plus* according to patients, families and healthcare providers (Adoption, Implementation)To assess the fidelity of delivery of *Care Plus* according to core components of the intervention (content, follow-up, GP case conference) (Adoption, Implementation)To assess the impact of *Care Plus* implementation of the total cost of healthcare utilisation (including hospitalisation, Emergency Department presentation, ambulatory care, general practitioner use, medications) in the last 3 months of life (Effectiveness)To develop an Implementation package of recommended approaches and effective strategies to establish *Care Plus* in other settings (Maintenance)

#### Core hypotheses

The implementation of *Care Plus* will reduce the acute hospitalisation days in the last 90 days of life by 25% for patients with advanced cancer.The implementation of *Care Plus* will increase by 25% the proportion of patients with advanced cancer referred to palliative care ≥90 days before death.*Care Plus* will decrease by 25% the proportion of patients experiencing more than 1 indicator of poor quality end of life care defined as: (≥ 2 acute hospital admissions, length of stay ≥14 days, ≥2 Emergency Department presentations in the last month of life, chemotherapy in the last 14 days of life, late or absent palliative care referral, and death in acute hospital) [41].*Care Plus* will be acceptable to patients, families and health professionals*Care Plus* will be delivered according to core components detailed (Table 2) in ≥50% of patients.*Care Plus* will reduce the total health system costs incurred in last 3 months of life.An Implementation Package will enable *Care Plus* to be scaled to other health services nationally and with international implications.

**Table 2 Tab2:** *Core Components of Care Plus*

1. **Palliative care is introduced at cancer-type specific key transition points**	
2. **Initial hospital-based palliative care consultation (as inpatient or outpatient), addressing:** • Review of underlying disease management • Screening for symptom distress • Screening for psychological distress • Review of informal community supports, including local community palliative care • Providing information • Advance care planning discussions • Involvement of family carer, including enquiry of concerns and needs of information	
3. **Regular, prescribed outpatient follow up:** • At minimum monthly for at least 2 months • At conclusion of the prescribed intervention, a clinical decision is made between the patient and palliative care physician for individualized follow-up beyond standard ‘dose’.	
4. **Case conference with the general practitioner within 28 days, addressing:** • Current and anticipated problems • Recommended management and therapies	

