### Implementation of care plus as practice change phase

During the practice change phase, all patients with targeted cancers reaching transition point will, by default, receive *Care Plus* as part of a hospital wide practice change.

A series of cancer-specific standard operating procedures for the implementation of *Care Plus* will be developed, including the steps of:
Identification of eligible patients reaching ‘transition point’ and process of alerting clinician;Discussion with patient and family by treating clinician/clinical team member;Provision of written information to patient and family;Delivery of *Care Plus* (as operationalised in Table 2):
Consultation by palliative care physician/clinical team member at or within 6 weeks of transition point.Prescribed follow up with details of the consultation recorded using domains of PC-NAT [43].General Practitioner Case Conference.

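### The hypothesis 3 quality composite counts late or absent palliative care referral, which Care Plus changes directly, so part of any fall can come from referral alone

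*Protocol article*

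**What the plan says.** Under Core hypotheses, the third hypothesis is that Care Plus "will decrease by 25% the proportion of patients experiencing more than 1 indicator of poor quality end of life care". Six indicators follow. Three concern acute use (admissions, length of stay, emergency presentations). The others are "chemotherapy in the last 14 days of life, late or absent palliative care referral, and death in acute hospital". 'Late' is not defined there.

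Referral is also the intervention. The first core component in Table 2 is "Palliative care is introduced at cancer-type specific key transition points". In the practice change phase "all patients with targeted cancers reaching transition point will, by default, receive" Care Plus, with "Consultation by palliative care physician/clinical team member at or within 6 weeks of transition point".

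Referral timing has its own hypothesis, the second: Care Plus "will increase by 25% the proportion of patients with advanced cancer referred to palliative care ≥90 days before death". The objective that hypothesis 3 serves is "To improve quality of end of life care for patients with cancer, with reduced acute health system use (Effectiveness"), and Table 3 also classes it under Effectiveness.

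The Background reports usual-care rates: "Patients in this cohort had at least one (83%) or two or more (38%) indicators of poorer quality of end of life care". Its definition there covers acute-use items only, with no referral item.

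**The concern.** The endpoint contains delivery of the intervention as one of its items. Because the cut is at more than one indicator, a timely referral reclassifies every patient who has the referral item plus exactly one other, even when admissions, length of stay, emergency presentations, chemotherapy and place of death are as before. The same event then counts towards hypothesis 2 (Reach) and again towards hypothesis 3 (Effectiveness).

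What is at stake is interpretation. A positive hypothesis 3 would be reported as better end-of-life care with less acute use, when an unknown share of the fall may only show that the referral pathway was working.

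**Working it through.** The article gives no baseline rate, sample size or power for the six-item endpoint, so there is no stated figure to reproduce. The power calculation concerns acute hospital days. The check asks how far the composite moves when only referral changes. The 25% is read as a relative fall.

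**Inputs from the Background**
- Acute-use indicators: at least one 83%, two or more 38%. So exactly one 0.83 − 0.38 = 0.45, and none 0.17.
- No palliative care in the last year: 1 − 0.59 = 0.41.
- Among those with access, median first contact 27 days before death. Absent or within 27 days: 0.41 + 0.59 × 0.5 = 0.705.
- For 61% (read as a share of those with access), first contact was in the final admission. Absent or final admission: 0.41 + 0.59 × 0.61 = 0.77.
- Death in an acute setting 57%, read as a share of all deaths.

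**Formula.** With q the proportion late or absent, assumed independent of the other items:

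P(more than 1) = P(two or more others) + P(exactly one other) × q.

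**Four items only (acute use and referral)**
- q = 0.77: 0.38 + 0.45 × 0.77 = 0.7265.
- q = 0.37: 0.38 + 0.45 × 0.37 = 0.5465, a relative fall of 24.8%.

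This is about the whole target, but it leaves out two of the protocol's six items.

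**Adding acute death at 57%, independent, late chemotherapy set to zero**
- Two or more others: 0.38 + 0.45 × 0.57 = 0.6365.
- Exactly one other: 0.45 × 0.43 + 0.17 × 0.57 = 0.2904.
- q = 0.77: 0.6365 + 0.2904 × 0.77 = 0.8601.
- q = 0.37: 0.6365 + 0.2904 × 0.37 = 0.7439.
- Relative fall: 1 − 0.7439/0.8601 = 13.5%.
- q needed for 25%: (0.75 × 0.8601 − 0.6365)/0.2904 = 0.03.
- From q = 0.705, clearing the item completely gives 1 − 0.6365/0.8412 = 24.3%, just short of 25%.

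**Sensitivity**
- *Late chemotherapy at 20% (assumed), independent.* Two or more others 0.6365 + 0.2904 × 0.2 = 0.6946; exactly one 0.2904 × 0.8 + 0.0731 × 0.2 = 0.2469, where 0.0731 = 0.17 × 0.43. The move from 77% to 37% gives 11.2%, and complete clearing gives 21.5%.
- *57% read as a share of the 80% who die in hospital.* Acute death is 0.80 × 0.57 = 0.456. The move from 77% to 37% gives 15.5%, and 25% needs q of about 0.12.
- *Overlap of acute death with the acute-use items, no chemotherapy.* The last two columns are for q from 0.77 to 0.37 and for complete clearing from 0.77.

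| Where the 57% of deaths fall | Two or more others | Exactly one other | 77% to 37% | Clearing |
|---|---|---|---|---|
| First in those with two or more, then those with one | 0.57 | 0.26 | 13.5% | 26.0% |
| In those with two or more (0.38), those with none (0.17), the remaining 0.02 in those with one | 0.40 | 0.60 | 27.8% | 53.6% |
| All those with exactly one (0.45), then 0.12 of those with none or with two or more; shown for none | 0.83 | 0.12 | 5.2% | 10.0% |

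- *At the hypothesis 2 target.* Read 'late' as under 90 days and assume 10% timely at baseline (q = 0.90). A rise of 25 percentage points (q = 0.65) gives 14.3% on four items, 8.1% with acute death independent, and 16.0% under the second overlap pattern. A 25% relative rise (q = 0.875) gives 1.4%, 0.8% and 1.6%.

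**Without the referral item**, a change in referral alone moves the endpoint by exactly 0%.

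**The case against.** The strongest defence is that the overlap is modest and partly guarded. With acute death included and independence, referral alone reaches 25% only if late referral is almost eliminated. The protocol does not expect that: hypothesis 5 looks for full core delivery in at least half of patients, and referral alone falls short of 25% at the hypothesis 2 target under the assumptions above. Delivery is tied to the transition point and not to death, so a patient who reaches that point close to death can still count as late. Hypothesis 3 is secondary. If only referral moved, the primary outcome of acute days should show no reduction beside it. The indicator set is cited from the literature, and earlier palliative care is arguably better care in itself. The Background also links earlier engagement to less hospital death and fewer emergency presentations, so referral changing with everything else fixed is a hypothetical.

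Most of this stands as a limit on size. A reader might infer that hypothesis 3 can be met simply by switching on the default referral, with no change in end-of-life care. The documents do not support that. Default delivery does not guarantee a timely referral, earlier palliative care is itself a change in care, and the full 25% comes easily only if acute death and chemotherapy are ignored or under a particular overlap.

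The defence does not remove the interpretive problem. A set suited to describing usual care can be unsuited to testing an intervention that supplies one of its items. Nor is this a detail left to an analysis plan, since the article itself fixes the six items and the threshold.

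**Conclusion.** The point holds as a limit on what hypothesis 3 can show. Part of any fall in the composite can arise from referral with the other five indicators unchanged, so the fall cannot by itself be read as better quality with reduced acute use.

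The size is not fixed by the article. For late or absent referral falling from 77% to 37%, the contribution is about 13.5% with acute death at 57%, no late chemotherapy and independent items; the overlap patterns tried give roughly 5% to 28%. The 25% target by referral alone usually needs near-complete clearing. These figures rest on rates for Victorian cancer inpatients, on proxies for the undefined 'late', and on referral being independent of the other indicators. The interpretive conclusion does not depend on them. As this is a secondary hypothesis, the change is one that should be made, not one on which the trial stands or falls.

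**What to change.** - Base the effectiveness conclusion for hypothesis 3 on the five indicators without the referral item; hypothesis 2 already covers referral. At minimum, prespecify the five-item version beside the six-item one and require the two to agree before claiming improved quality with less acute use.
- Define 'late' for the referral item, and say whether it is the complement of the 90-day criterion in hypothesis 2.
- Report each of the six components by period.

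The cost is wording in the protocol or analysis plan. No new data are needed, since all items are required for the six-item version anyway. The downside is that the five-item version departs from the cited set, so both should be tabulated.

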## Methods

### Study design

This study is a stepped-wedge implementation trial of early palliative care for patients with advanced cancer (Fig. 1). This design includes a series of phases: (1) control periods when usual care is observed while phases of planning and engagement occur, (2) practice change periods when *Care Plus* is administered, and (3) maintenance periods, when an evaluation phase enables measurement of ongoing impact and sustainability in cancer care.

**Fig. 1 Fig1:**
[figure not shown]
Multisite stepped-wedge implementation trial of early palliative care for patients with advanced cancer

### Study setting

This study is being undertaken at four metropolitan tertiary cancer services in two Australian states. These hospitals have specialist palliative care providing both inpatient and outpatient consultation services.

### Implementation framework

Consistent with the Consolidated Framework for Implementation Research (CFIR), this study reconciles scientific rigor with the pragmatism required to achieve successful change in complex systems by taking into account multiple dynamics and influences upon the implementation process. Understanding the internal and external context of each clinical site including its structural characteristics, culture, divisions, readiness for implementation and external policies are fundamental to the implementation framework. Equally important are the individuals (including patients and health providers), the characteristics of the intervention and the overall implementation process itself which involves phases of *planning, engagement, practice change and evaluation* [42].

